## 3 Study objectives

**The overarching aim** of this study is to investigate the effect of a 6-week intervention with two different probiotic products ((*Lactobacillus reuteri* ATCC PTA 6475 och Gastrus (*Lactobacillus reuteri* DSM 17938/ATCC PTA 6475)) on the intestinal permeability of diarrhoea-predominant IBS (IBS-D) patients.

**The primary endpoint** is the difference in small intestinal permeability, measured as the urinary lactulose/rhamnose secretion ratio, after a 6-week intervention with the probiotic products compared to the placebo product, in IBS-D patients.

**Secondary endpoints** are the differences between intervention with the probiotic products compared to the placebo in IBS-D patients on:

- The small intestinal permeability, measured as the urinary lactulose/rhamnose secretion ratio, after 3-week intervention
- Whole gut permeability measured as urinary sucralose/erythritol excretion ratio (0-24hrs) after 3 and 6 weeks
- Colonic permeability measured as urinary sucralose/erythritol ratio (5-24hrs) after 3 and 6 weeks
- Gastroduodenal permeability measured as urinary sucrose excretion (0-5hrs) after 3 and 6 weeks
- Various potential biomarkers of general intestinal barrier function and inflammation in blood and faecal samples after 3 and 6 weeks such as plasma i-FABP, faecal zonulin, serum zonulin, bacterial 16S ribosomal RNA (16S rRNA) gene copy number (whole blood), plasma vasoactive intestinal polypeptide (VIP), plasma high-sensitive C-reactive protein (hs-CRP), faecal calprotectin and plasma cytokines (e.g. IL-6 and IL-10)

**Exploratory endpoints** are the effects of the intervention with the probiotic products in comparison to the placebo in IBS-D patients on:

- Stool frequency and consistency (Daily diary on bowel movement using Bristol Stool Chart)
- Gastrointestinal symptoms as measured by the GSRS-IBS and IBS-SSS after 3 and 6 weeks
- Quality of life after 3 and 6 weeks (5Q-5D-5L, IBS-QOL)
- Perceived stress after 6 weeks (using the Perceived stress scale, PSS)
- Anxiety and depression symptoms after 3 and 6 weeks (HADS)
- Cortisol awakening rhythm (saliva) after 3 and 6 weeks
- Intestinal microbiota composition (16S rRNA-based next generation sequencing of faecal samples) after 3 and 6 weeks
- Metabolomic profile of faecal samples and blood, including SCFA metabolism and tryptophan catabolites such as 5-HT and melatonin, after 3 and 6 weeks.

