#### 4 Study design

This will be a single-centre, randomised, double-blinded, placebo-controlled intervention study with a parallel design and three study arms.

The study will investigate the effects of supplementation with the probiotic products *L. reuteri* ATCC PTA 6475 and Gastrus (*L. reuteri* DSM 17938/ATCC PTA 6475) on the intestinal barrier function, gut health and stress symptoms in diarrhoea-predominant IBS (IBS-D) patients. The test product is a tablet containing either ATCC PTA 6475 or Gastrus (DSM 17938/ATCC PTA 6475). The subjects will consume the product twice a day, giving a daily dose of  $1 \times 10^9$  CFU of each strain. The placebo product is an identical tablet except for the absence of probiotics. After having given their written informed consent, subjects will complete screening procedures to evaluate their eligibility for the study (visit 1). Study participants will undergo two baseline visits (visits 2 and 3, 3 weeks apart) to account for individual variations, and will then be randomly assigned to 6-week intake of either ATCC PTA 6475, Gastrus, or placebo in a ratio of 1:1:1 (stratified by sex). Participants will attend a study visit three weeks into the intervention (visit 4) and at the end of the intervention (visit 5, week 6). The intestinal permeability will be assessed using a standardized multi-sugar test at visit 2, visit 3, visit 4, and at end of intervention (visit 5). Blood, saliva and faecal samples will be collected at visit 2-5. In addition, gastrointestinal symptoms will be recorded at those visits (using GSRS-IBS, IBS-SSS). Quality of life using the 5Q-5D-5L and Hospital Anxiety and Depression Scale (HADS) scores will also be recorded at those visits. In addition, at visit 3 and visit 5, the IBS-QoL and the Perceived Stress Scale (PSS) will be completed. In a daily diary, participants will record stool frequency and consistency from visit 2 until end-of-study visit 5. Dietary habits of the patients will be assessed via a food frequency questionnaire (FFQ) and a 3-day food diary before the intervention (between visit 2 and 3).

During the entire run-in and intervention period, the subjects will be asked not to consume any probiotic products other than the study products. During the entire study subjects should maintain their habitual diet and life style such as physical activity level and sleep habits.

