## 5 Study population

### 5.1 Number of subjects

The sample size is based on the ability to find a significant lactulose/rhamnose ratio difference between one of the probiotic study arms and the placebo arm. A relevant change of 15% in lactulose/rhamnose difference should be detected as significant, which according to the study by Zuhl et al. 2014 amounts to 0.009 points in ratio difference.

The sample size calculation is based on the following assumptions:

- 80% power
- An expected SD of 0.01 (Zuhl et al. 2014)
- Significance (alpha) level of 5%
- Two-sided testing (significance level of 5%)

To account for a potential drop-out rate of 15%, a total of 75 subjects will be randomized (N=25 subjects in each group should be included).

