### 6.4 Randomisation

Randomisation will be computerised by an independent researcher. A third party not otherwise involved in the study will label the active and placebo study products. Randomisation lists will be kept in sealed envelopes at the study sites and a sealed copy will also be kept at Sponsor site. The envelopes may not be open until all study data have been entered into the database and until the database has been locked. For exceptions, see “Serious Adverse Event” below. Randomisation will be stratified by gender. At screening, subjects will be assigned a screening number starting at 1001, according to their chronological entry into the study. As an example the first subject will have screening number 1001. If the subjects are suitable for study participation, they will receive their randomization number at Visit 1. Randomisation numbers will include the stratification number (Female = 5; Male = 9), and will be allocated sequentially in the order in which the subjects finalise Visit 1. For example, the first female included will receive the randomization number: 5001, whereas the fifth male included will receive the randomisation number: 9005.

Subjects will be asked to return the used packages from the Study Products to allow assessment by the investigator of compliance. The investigators will also assess compliance by a daily checklist distributed to the participants and by interviews at every visit.

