## **12 Data management and statistical analysis**

The investigators will ensure that the subject's anonymity will be maintained. On all documents, subjects will be identified only by a subject number – not by their names or personal number.

All statistical tests will be assessed using a nominal two-sided significance level of 5%.

The primary efficacy analysis will be based on difference in lactulose/rhamnose ratio before and after intervention for the two probiotic strains as compared to placebo. The difference between before and after intervention observed in either of the two probiotic strains will be compared to that difference observed for the placebo arm of the study using the two-sided Mann-Whitney U-test for independent samples (as in Zuhl et al. 2014 and similar studies).

Biomarker levels studied in plasma, serum and stool samples will be evaluated on log-scale, where appropriate, using the appropriate non-parametric univariate tests (e.g. Wilcoxon signed-rank test, Mann-Whitney U-test), as well as multivariate analyses using appropriate cross-validation approaches (as detailed in the SAP). Questionnaires will be evaluated using both logistic regression analyses of responder proportions as well as ANOVA for original response values. Microbiota phylogenetic profiles (NGS results) will be assessed by both uni- and multivariate analyses on the species- and genus-like phylogenetic levels, as well as on in-depth functional levels based on whole genome shotgun sequencing (NGS results).

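### The primary Mann-Whitney test on before-after differences is valid but adjusts for neither baseline nor sex; the precision given up equals about 1-5 patients per arm if the two baselines are averaged, about 9-13 if only one is used

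*Protocol*

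**What the plan says.** Section 3 of the protocol defines the primary endpoint as the difference in urinary L/R ratio "after a 6-week intervention with the probiotic products compared to the placebo product". Section 12 turns this into a change score: "The primary efficacy analysis will be based on difference in lactulose/rhamnose ratio before and after intervention". The change in a probiotic arm "will be compared to that difference observed for the placebo arm of the study using the two-sided Mann-Whitney U-test for independent samples". No covariate or stratum is named. The section's only reference to a SAP is attached to the multivariate biomarker analyses.

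Section 4 explains why permeability is measured twice before treatment: "Study participants will undergo two baseline visits (visits 2 and 3, 3 weeks apart) to account for individual variations". Table 1 and Section 6.6 place a full multi-sugar test at both visits. Section 12 does not say whether 'before' is visit 2, visit 3 or their mean.

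Section 6.4 states: "Randomisation will be stratified by gender". Sex does not appear in the primary analysis.

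**The concern.** The design pays for information that the primary analysis, as written, does not clearly use. Each participant completes two 24-hour urine collections before treatment, and randomisation is balanced on sex. Yet the named test takes neither the baseline level nor sex into account.

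Subtracting a baseline is equivalent to fixing its regression slope at 1. When visits are only moderately correlated, that slope is too steep and adds noise; analysis of covariance estimates the slope instead. If the baseline subtracted is a single visit, all of that visit's measurement noise also goes into the result. At stake is precision in a trial of 25 randomised patients per arm whose power is only just at its 80% target.

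**Working it through.** **The plan's own figure.** Section 5.1 gives an effect of 0.009, an SD of 0.01, two-sided 5%, 80% power and 15% drop-out, with 25 per arm.
- Normal formula: n = 2 × (1.960 + 0.842)² × (0.01/0.009)² = 19.4.
- Dividing by 0.955, the efficiency of the Mann-Whitney test for normal data, gives 20.3, rounded up to 21. A t-test calculation also gives 21.
- 21/0.85 = 24.7, rounded up to 25. The stated size reproduces.
- Completers: 25 × 0.85 = 21 per arm.

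**Residual variances.** Assume equal variance (set to 1) and equal correlation r between any two visits. The protocol gives no r, so 0.3, 0.5 and 0.7 are assumptions.
- Change from one baseline visit: 2(1 − r)
- Change from the mean of two baselines: 1 + (1 + r)/2 − 2r = 1.5(1 − r)
- Analysis of covariance on the mean of two baselines: 1 − 2r²/(1 + r)

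The gain in patients per arm is 21 × (variance of change score / variance of covariance model − 1).

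| r | Change, one visit | Change, mean of two | Covariance model | Gain if 'before' is one visit | Gain if 'before' is the mean |
|---|---|---|---|---|---|
| 0.3 | 1.40 | 1.05 | 0.862 | 13.1 | 4.6 |
| 0.5 | 1.00 | 0.75 | 0.667 | 10.5 | 2.6 |
| 0.7 | 0.60 | 0.45 | 0.424 | 8.8 | 1.3 |

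Example at r = 0.5: 21 × (1.00/0.667 − 1) = 10.5 and 21 × (0.75/0.667 − 1) = 2.6.

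**How much comes from averaging alone.** 2(1 − r) / 1.5(1 − r) = 4/3 at every r, so 21 × (4/3 − 1) = 7 patients per arm without changing the test.

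**Sensitivity.**
- Adding the 0.955 rank-test efficiency (normal data) raises the last column to 5.8, 3.7 and 2.4.
- Outside the assumed range, the two gains are 15.0 and 6.0 at r = 0.2, and 7.5 and 0.4 at r = 0.9.
- Section 10 replaces non-completers. With 25 completers per arm, the gains become 15.6, 12.5 and 10.4 (one visit) and 5.5, 3.1 and 1.6 (mean).

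**Simulated power** (6,000 runs, 21 per arm, effect of 0.9 SD of the one-visit change; the covariance model includes sex, but no sex effect was simulated):

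| Data | r | Mann-Whitney, one visit | Mann-Whitney, mean of two | Covariance model |
|---|---|---|---|---|
| Normal | 0.5 | 0.80 | 0.89 | 0.93 |
| Normal | 0.7 | 0.78 | 0.89 | 0.92 |
| Skewed (assumed log-SD 0.5) | 0.5 | 0.66 | 0.78 | 0.93 (log scale) |
| Skewed (assumed log-SD 0.5) | 0.7 | 0.67 | 0.79 | 0.91 (log scale) |

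The normal rows read the protocol's SD of 0.01 as the SD of a one-visit change, which Section 5.1 does not specify. The skewed rows are not calibrated to the 15% target and show only the ordering of the methods. None of the rows measures what adjusting for sex would add.

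**The case against.** The strongest defence is that the rank test is prespecified, valid and consistent with the sample size, in a trial that Section 10 calls proof-of-concept. That stands: this is a matter of efficiency, not an error. Several stronger readings are tempting, and the protocol does not support them.

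- *The second baseline is thrown away.* Section 12 does not say so. Section 4's stated purpose fits averaging at least as well, and a SAP that is not shown may define the baseline. Hence both cases are computed.
- *The test is invalid because it ignores the stratification factor.* Leaving sex out costs precision and tends to make the test conservative; it does not inflate the type I error.
- *Regression to the mean biases the comparison.* The eligibility criteria in Section 5.3 do not select on L/R, so it is expected equally in all randomised arms. Chance baseline imbalance affects precision, not the error rate.
- *A relative target is tested on an absolute scale.* Section 5.1 itself converts its 15%, which "amounts to 0.009 points in ratio difference", so the test matches the design calculation.
- *The change is free.* It needs no new data, but it adds linearity and distributional assumptions and replaces a rank comparison with a ratio of geometric means.

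**Conclusion.** The point holds as an improvement in precision. The protocol itself fixes an unadjusted test, and the covariance model was more precise in every scenario computed. The size depends on two things the protocol does not give: which visit or visits make up 'before', and the between-visit correlation. With 21 completers per arm and an assumed r of 0.3 to 0.7, the gain is about 9-13 patients per arm for a single-visit baseline, 7 of them from averaging alone. It is about 1-5 per arm if the baseline is already the mean. A reader might take 9-13 as the price of the Mann-Whitney test itself; it is not, because most of it is the price of using one baseline visit instead of two. No figure is claimed for adjusting for sex.

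**What to change.** 1. In Section 12, define 'before' as the mean of visits 2 and 3, with a rule for when one of the two is missing.
2. Before unblinding, make the primary analysis a linear model for week-6 log(L/R) with treatment, the mean of the two baseline log(L/R) values, and sex. This also answers the endpoint as Section 3 words it, which is the between-arm difference after six weeks.
3. Report each product-versus-placebo ratio of geometric means with a 95% CI.
4. Keep the Mann-Whitney test on the before-after difference, using the same definition of 'before', as a sensitivity analysis.

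The cost is protocol and SAP wording only, since the planned visits already supply every variable. The price in method is the added model assumptions, which the log scale eases, and the change of estimand, which should be stated openly. If the sponsor prefers to keep the rank test as primary, step 1 alone secures the 7 patients per arm that averaging brings over a single-visit baseline.

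### Section 12 lists a within-arm signed-rank test for biomarkers without saying that only the between-arm test answers Section 3, and names no baseline term for the questionnaire ANOVA

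*Protocol*

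**What the plan says.** Section 3 of the protocol frames both endpoint families against placebo. The secondary endpoints, which include the blood and faecal biomarkers, "are the differences between intervention with the probiotic products compared to the placebo in IBS-D patients on" the listed measures. The exploratory endpoints, which include the questionnaires, "are the effects of the intervention with the probiotic products in comparison to the placebo in IBS-D patients on" their own list.

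Section 12 sets one two-sided 5% level for all tests and then treats the outcome groups differently:

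- Primary: "The primary efficacy analysis will be based on difference in lactulose/rhamnose ratio before and after intervention for the two probiotic strains as compared to placebo". Each product arm's before-after difference is compared with that in the placebo arm by Mann-Whitney U-test.
- Biomarkers in plasma, serum and stool: log scale where suitable, with suitable univariate non-parametric tests, "e.g. Wilcoxon signed-rank test, Mann-Whitney U-test". The sentence continues: "as well as multivariate analyses using appropriate cross-validation approaches (as detailed in the SAP").
- Questionnaires: "Questionnaires will be evaluated using both logistic regression analyses of responder proportions as well as ANOVA for original response values".

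The biomarker and questionnaire sentences mention neither placebo nor a baseline term.

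Baseline data exist. Section 4 states: "Study participants will undergo two baseline visits (visits 2 and 3, 3 weeks apart) to account for individual variations". Table 1 places blood and faecal sampling, GSRS-IBS, IBS-SSS, the EuroQol questionnaire and HADS at both baseline visits, and IBS-QOL and PSS at visit 3 only. Randomisation is stratified by sex.

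**The concern.** A signed-rank test needs paired values. In a parallel three-arm trial no patient is paired with a placebo value, so the test can only compare visits within one arm. It then responds to anything that moves that arm over time, such as a shared time trend or assay drift, as readily as to the product. The Mann-Whitney U-test named beside it can compare a product arm with placebo. Section 12 lists the two together at the same 5% level and does not say which one answers Section 3. A report could follow this text and present a significant before-after change in a product arm as a result on a secondary endpoint.

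The questionnaire issue is a different and milder one. The protocol takes two baselines because individuals vary, and its primary analysis uses before-after differences. The questionnaire ANOVA is named without any use of baseline. If it is run on follow-up scores alone, stable differences between persons stay in the error term of a small trial.

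**Working it through.** **Numbers per arm.** The plan's own figure is used only to set the number of completers. Section 5.1 gives a difference of 0.009, SD 0.01, two-sided 5%, 80% power and 15% drop-out. Normal formula: 2 × (1.960 + 0.842)² × 0.01² / 0.009² = 19.4, so 20 per arm. The t-test version gives 20.4, so 21 per arm, and 21 / 0.85 = 24.7, so 25. The stated 25 per arm is reproduced. Conversely 25 × 0.85 = 21.25, so about 21 completers per arm. Section 10 replaces non-completers, so the number may be higher; the variance ratios below do not depend on it.

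**Within-arm versus between-arm test.** Simulation, 4,000 runs: two arms of 21 with identical normal changes from baseline, so no product effect. The shared shift, in SDs of change, is assumed.

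| Shared shift | Signed-rank significant in the product arm | Product arm significant, placebo not | Mann-Whitney between arms |
|---|---|---|---|
| 0 | 4.1% | 3.8% | 4.6% |
| 0.3 | 24% | 18% | 4.7% |
| 0.5 | 56% | 24% | 5.3% |

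The between-arm test holds its level. The within-arm test, read as evidence for the product, does not.

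**Baseline adjustment for questionnaires.** Let r be the correlation between any two visits, with equal variances. The documents give no value, so r is assumed and shown over a range. Relative to follow-up scores alone (variance 1):

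- adjusted for one baseline: 1 − r²
- adjusted for the mean of two baselines: that mean has variance (1 + r)/2 and covariance r with follow-up, so the residual variance is 1 − 2r²/(1 + r)

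The difference detectable with 80% power and 21 per arm, on follow-up scores alone, is (1.960 + 0.842) × √(2/21) = 0.865 SD. Multiply by the square root of the residual variance for the adjusted analysis.

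| r | One baseline: variance (cut) | Detectable, SD | Two baselines: variance (cut) | Detectable, SD |
|---|---|---|---|---|
| 0.3 | 0.91 (9%) | 0.825 | 0.862 (14%) | 0.803 |
| 0.5 | 0.75 (25%) | 0.749 | 0.667 (33%) | 0.706 |
| 0.7 | 0.51 (49%) | 0.617 | 0.424 (58%) | 0.563 |
| 0.8 | 0.36 (64%) | 0.519 | 0.289 (71%) | 0.465 |

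For r between 0.5 and 0.7, the gain equals 1/0.75 = 1.3 to 1/0.51 = 2.0 times the patients with one baseline, and 1/0.667 = 1.5 to 1/0.424 = 2.4 times with two. The small loss of degrees of freedom for the covariate is ignored.

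**The case against.** The case against has several parts, and much of it stands.

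- The between-arm test is already named. Mann-Whitney stands next to the signed-rank test, both are only examples, and they apply to biomarkers alone. A reader might infer that the secondary and exploratory endpoints in general lack a placebo comparison. The text does not support that: the signed-rank test is not assigned to the permeability ratios, the questionnaires or the microbiota.
- ANOVA and logistic regression both compare randomised arms, and a three-arm ANOVA allows product-versus-placebo contrasts. A reader might infer that the questionnaire analysis is invalid or misses placebo. It is not invalid; without baseline it is only less precise.
- A reader might also infer that baseline is deliberately discarded. The phrase contrasts the full score with a responder cut-off and most naturally means the undichotomised score. A change-score or repeated-measures ANOVA is not excluded.
- The IBS-SSS entry threshold of 75 might be cited for regression to the mean. It does not bear on biomarkers, on which nobody is selected. Eligibility is also assessed at visit 1, before both baselines, so part of any such regression would occur before baseline.
- Covariates and contrasts commonly sit in the SAP, which is not at hand, so their absence from the protocol is no error in itself.

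Two things remain. The protocol itself names a test that cannot answer Section 3 and does not mark it as descriptive; the pointer to the SAP is attached to the multivariate analyses. It also names a questionnaire method that a better one, using data already collected, can replace.

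**Conclusion.** The point holds as a matter of interpretation and precision for secondary and exploratory endpoints; the primary analysis is not affected.

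For biomarkers, a signed-rank result cannot support the comparison with placebo. With a shared shift of 0.3 to 0.5 SD of change, it would be significant in 24% to 56% of trials with no product effect. This rests on an assumed shift and normal changes, and it causes harm only if within-arm results are presented as efficacy, which the protocol neither states nor rules out.

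For questionnaires, the stated ANOVA is a valid comparison of randomised arms. Adjustment for baseline would cut error variance by 25% to 49% with one baseline and by 33% to 58% with the mean of two, if the correlation is 0.5 to 0.7. Over 0.3 to 0.8 the ranges are 9% to 64% and 14% to 71%. These correlations are assumptions.

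**What to change.** In Section 12, and in the SAP to match:

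1. State that inference for biomarkers and questionnaires rests on each product-versus-placebo contrast, reported with a 95% CI, and that signed-rank tests are descriptive only.
2. Replace the ANOVA on unadjusted questionnaire scores with ANCOVA, or a repeated-measures model, adjusted for sex and for the baseline score: the mean of visits 2 and 3, or visit 3 for IBS-QOL and PSS.
3. Analyse log-scale biomarkers in the same way, or by Mann-Whitney on change from baseline. If change is used, take it from the mean of the two baselines. Under the same assumptions its variance is 1 + (1 + r)/2 − 2r = 1.5(1 − r), against 2(1 − r) from a single baseline. At r = 0.5 that is 0.75 against 1.0.

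The cost is wording and a little analysis work. No visit, sample or patient is added, because all the baselines are already scheduled.
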